### Who will take informed consent? {26a}

Patients will be introduced to the trial by the research team. This team will answer any questions during an in-person meeting. The primary investigator will provide information sheets about the proposed trial to all participants. The research team members will discuss the trial with the participants in light of the information provided in the information sheets. The patient will then be able to engage in an informed discussion with the primary investigator. The primary investigator will obtain the signed written consent from the patients interested in participating in the trial. The consent form will include details such as the study’s title, investigators’ names, registered information, research background, how the study will be conducted, what participants are expected to do in the study, treatment plans, and obligations. The information sheets and patient consent forms will be translated into Hindi and shared with the participants if they do not understand English.

### Interventions

#### Explanation for the choice of comparators {6b}

The control group populations comprising the no-pain population and CS-positive patients with CLBP will help determine the effectiveness of interventions and allow us to gather valuable information for a better understanding of the impact of endogenous analgesia on pain control. The choice of a comparator is further strengthened by the results of recent recommendations that clinicians should employ standard education strategies, including exercise and physical activity, for CLBP patients [30].

#### Intervention description {11a}

All patients who report for CLBP management will be continuously enrolled in the study. They will undergo a standardized history taking for recording of their demographic details and will be screened for eligibility. The first author will conduct a complete physical assessment and neurological examination, and the presence of “red flags” will be closely monitored. The patients providing voluntary informed consent will be referred to the outpatient departments (OPDs) of the concerned study center where more detailed evaluations will be conducted.

In case of any doubt about a participant’s capacity to engage in the exercise program, they will be directed to a medical professional for an evaluation. The same process will continue until all participants have been recruited (*n* = 172). The recruited participants will then be randomized to receive one of the three exercise interventions along with patient education or patient education alone. A group comprising healthy volunteers will serve as the control group. The interventions will last for 12 weeks. Follow-up will be conducted 3 and 6 months after the intervention.

Three qualified physiotherapists (PTs) in each center will provide the interventions. All of them have a postgraduate degree in musculoskeletal physiotherapy and an average of 11 years of clinical experience. Before initiation of the study, they will attend a training session discussing the detailed treatment procedures. All PTs will be instructed to adhere to the treatment checklist provided and to complete treatment notes after each session. The participants will be instructed to avoid engaging in any other physical program during the study period and to not exercise at home during the intervention period. All the three participant groups will receive the targeted exercise interventions along with the same health education provided to group 4 participants. In order to manage time as effectively as possible, every exercise group will have 5–7 participants. The participants will be advised to continue the exercises after the treatments are over in order to support self-management.

Group 1 (AE group): This group will be subjected to a comprehensive stretching routine (lower limbs, upper limbs, and spine for 30 s in each section), 20–40 min of treadmill walking (intensity adjusted based on individual capacity and pain reports), and a 5-min local massage to relax [31]. Each walking session will start with a 5-min warm-up at a self-determined speed, followed by 20–40 min of intensive walking, and finally, a 5-min cool-down at a self-selected speed. The intensity of the walking exercise will be determined based on the heart rate and using the Borg scale. The maximum heart rate % will be calculated as 208 − (0.7 × age) [32]. The levels between 12 and 13 (moderate intensity) of the Borg scale and a range of 50–75% of maximum heart rate will be used.

Group 2 (MCE group): The first stage (1st–3rd sessions) will begin with isometric contraction of the local stability muscles (e.g., lumbar multifidus, transversus abdominis) through an abdominal drawing-in maneuver in minimally loading positions (supine lying, quadruped, sitting, and standing) [33]. The participants will be trained to activate the local stability muscles from the global muscles in an individualized manner [34]. In the second stage (4th–9th sessions), additional loads will be placed on the spine through various upper and lower extremities and trunk movement patterns to recruit various trunk [local and global] muscles. In the third stage [10th–12th sessions], functional movement patterns will be incorporated into the training program [33] (Fig. 2A–C). Exercise progression will be based on patient’s fatigue, pain thresholds, or observed movement control.

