**Methods:**

The trial is a randomized, controlled, multi-center study with four experimental groups and one healthy control group. Both the researchers and the people in the study will be blinded to the results. This paper describes the protocol for a trial examining the effects of 12-week individualized, twice-weekly exercise sessions lasting 30 to 60 min in persons with CLBP, who are positive for CS. Participants will be randomized to receive either patient education with motor control exercises (MCE), superficial strengthening (SS), aerobic exercises (AE), or patient education alone. Another group comprised of healthy volunteers will serve as controls. The primary outcomes are changes in CPM outcomes as measured by the cold pressor test (CPT). The secondary objectives are to evaluate executive functioning, pain, disability, quality of life, and spine muscle strength. The outcomes will be measured at 3 months and at a 6-month follow-up.

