### Sample size {14}

The sample size was calculated based on the inhibitory effect of the CPT on the PPT, assuming a standard deviation of 100 kPa for the inhibitory effect across all three exercise groups. A sample size of 30 participants per group provides 87% power for an independent *t*-test at a 2-sided alpha of 0.05 to detect a difference in inhibition of 80 kPa [17] when assuming a minimum difference of 0.47 (equivalent to 10% change) as clinically relevant for the CPM effect [55]. Therefore, anticipating a 30% dropout rate, 43 participants will be recruited for each group.

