### Statistical methods

#### Statistical methods for primary and secondary outcomes {20a,b}

The Shapiro–Wilk test will be used to assess the normality of the distribution of the data. A one-way analysis of variance (ANOVA) will be used to compare baseline characteristics between the groups. Descriptive statistics will be used to calculate the mean values of all outcome variables collected. A repeated measure ANOVA statistic will be used to evaluate the effect of three types of exercise interventions on CPM, neurophysiological outcomes, pain, disability, strength measures, and QoL. The study will use a 5 (between subjects – type of exercise interventions: AE vs. MCE vs. SS vs. patient education vs. no-pain control) × 3 (within subjects – time: before vs. after vs. 3 months after the intervention) mixed design. Tukey’s post hoc analysis will be conducted to establish differences between the groups. Effect size will be estimated by dividing the mean difference in outcomes between the intervention and control groups by the combined standard deviation of the two groups [56].

The primary outcome will undergo a per-protocol analysis. Pearson correlation analysis will be performed to determine the relationship between patient characteristics (Table 4), CPM, executive functioning, pain, strength measures, disability, and QoL. Multiple linear regression analysis will be used to deduce the characteristics of individuals responding positively to exercise interventions. For all measurements, *p* will be considered significant, if it is < 0.05. The data collected will be analyzed using SPSS (Statistical Program for the Social Sciences) 16.0 (IBM Corp., Armonk, NY).

**Table 4 Tab4:** Summary of patient characteristics to be collected

Characteristics	CLBP group	Control group
Age (years)	X	X
Gender (male/female)	X	X
Pain episode duration (weeks)	X	X
Body mass index (kg/m^2^)	X	X
Education level (yes/no; school incomplete, completed secondary school, completed diploma/completed bachelors and above)	X	X
Employment status (yes/no; employed (full or part-time), unemployed, retired)	X	X
Marital status (yes/no; married/separated/ divorced, single)	X	X
Personal behaviors Alcohol status (yes/no) Smoking status (yes/no)	X	X
Comorbidities	X	X
Fear avoidance behavior	X	X
Perception of improvement	X	X

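### Exercise is delivered in classes of 5–7, but the 87% power and the ANOVA treat participants as independent; any positive within-class correlation makes standard errors for exercise-arm comparisons too small

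*Protocol article*

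**What the plan says.** The Protocol article, Intervention description {11a}, states that "every exercise group will have 5–7 participants", for reasons of time management. It adds: "Three qualified physiotherapists (PTs) in each center will provide the interventions". It does not say whether a therapist works in one arm or several. The abstract describes "12-week individualized, twice-weekly exercise sessions".

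Trial design {8} randomises individual patients 1:1:1:1. Sample size {14} states: "A sample size of 30 participants per group provides 87% power". The test behind this figure is an unpaired t-test, two-sided at 5%; the target is 80 kPa and the SD is taken as 100 kPa. The only inflation is for 30% dropout, which gives 43 per group.

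Statistical methods {20a,b} states: "A repeated measure ANOVA statistic will be used to evaluate the effect of three types of exercise interventions on CPM" and the other outcomes. The factors are group (five levels) and time (three levels), followed by Tukey comparisons. Neither that section nor the missing-data section {20c} contains a class term, an ICC, a design effect or a robust variance.

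**The concern.** An arm of 43 cannot be a group of 5 to 7, so the sentence must describe classes inside each exercise arm. Classmates share sessions, an instructor and a peer group for 12 weeks, so their outcomes may be more alike than those of patients in different classes. Randomising individuals does not remove this, because the correlation arises after allocation and is nested within arm.

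The t-test behind the 87% and the planned ANOVA both count each participant as a full independent unit. With any positive within-class correlation, the estimated standard error of a difference involving an exercise arm is too small. The planned test then rejects too often when there is no difference. A test that holds its error rate at 5% has less power than stated. The primary objective compares exercise types with each other, which is where both compared arms are taught in classes.

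**Working it through.** **Inputs.** From Sample size {14}: 30 completers per group, difference 80 kPa, SD 100 kPa, two-sided alpha 0.05, 30% dropout, 43 recruited. From Intervention description {11a}: class size 5–7. The ICC is not in the document; 0.01 to 0.10 is assumed.

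**The stated figure.** The noncentrality is 80 / (100 × √(2/30)) = 3.098. Power is 87.3% by the normal approximation and 86.1% by the noncentral t with 58 df. The 87% therefore reproduces, with participants fully independent. 30 / 0.70 = 42.9, rounded up to 43, so nothing is added for clustering.

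**Classes per arm.** 43/7 = 6.1 and 43/5 = 8.6, so about 6 to 9. Taking seven classes, 30 completers give 30/7 ≈ 4.3 analysed per class.

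**Formulas.** Design effect DE = 1 + (m − 1) × ICC, with m the analysed class size. Type I error of the unadjusted test is about 2 × P(T > 2.002/√DE), with T on 58 df. Power with the error rate held at 5% uses the noncentral t with noncentrality 3.098/√DE.

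**Main case: m ≈ 4.3, both arms in classes**

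| ICC | DE | Type I error, unadjusted test | Power at held 5% (58 df) | Power at held 5% (12 df) |
|---|---|---|---|---|
| 0.01 | 1.033 | 5.4% | 85% | 80% |
| 0.02 | 1.066 | 5.7% | 84% | 79% |
| 0.05 | 1.164 | 6.9% | 81% | 75% |
| 0.10 | 1.329 | 8.8% | 75% | 69% |

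The last column uses class-level degrees of freedom, 2 × (7 − 1) = 12, the cautious end for a small-sample correction.

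**Upper case: five intact classes of six (m = 6).** At ICC 0.05, DE = 1.25, type I error is 7.9% and power 78%. At ICC 0.10, DE = 1.50, with 10.8% and 70%.

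**Only one compared arm in classes.** DE is replaced by (DE + 1)/2. At ICC 0.05 and m ≈ 4.3 this is 1.082, giving type I error of 5.9% and power of 83%. With intact classes of 5 to 7, the figures are 6.1–6.7% and 81–83%.

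**What the planned test itself would do.** The unadjusted test keeps its too-small standard error, so its rejection rate at 80 kPa falls little. Approximately Φ((3.098 − 2.002)/√DE), this is 86%, 85% and 83% at ICC 0.02, 0.05 and 0.10. A simulation with seven classes per arm (40,000 replicates) gave 85%, 84% and 83%.

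**The case against.** The strongest objection is that the ICC may be close to zero. The primary outcome is a change in pressure pain threshold taken by an independent blinded assessor, and exercise intensity and progression are adjusted to the individual. At ICC 0.01 the cost is about one point of power and type I error is 5.4%. This limits the size of the problem, but the protocol gives no ground for assuming zero, and the direction is the same for any positive value.

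It may also be said that an analysis plan or fuller protocol could deal with this. But the article itself fixes the class delivery, the independent t-test and the two-factor model, and these do not fit together.

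A reader might go further in four ways that the document does not support:

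- **Pairing the inflated type I error with the reduced power as features of one analysis.** They belong to different tests. The inflation belongs to the planned unadjusted test, and the power loss appears only when clustering is modelled or the error rate is held at 5%.
- **Taking five full classes of six as the base case.** The protocol's own 30% dropout leaves about 4.3 completers per class, so those figures are an upper case.
- **Concluding that therapist effects are mixed with arm effects.** The protocol does not say whether therapists are nested in arms. If each works across arms, a common therapist effect would not inflate error in this way.
- **Reading the abstract's description of the sessions as an error.** Tailoring within a small class is compatible with the intervention text, so this needs clarifying rather than correcting.

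**Conclusion.** The point holds for comparisons involving exercise arms. The protocol delivers exercise in classes but sizes and analyses the trial as if participants were independent. The direction is certain for any positive within-class ICC; the size rests on an assumed ICC. In the main case the effect is modest: type I error of about 5.4% to 8.8% instead of 5%, and power of about 85% down to 75% over ICC 0.01–0.10, with a further loss of roughly five to six points at class-level degrees of freedom. It is larger with intact classes of six and smaller where only one arm is taught in classes. The education section gives no class size, and the no-pain controls attend no class.

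These figures are for a single unadjusted two-arm test at one time point, as in the protocol's own power statement. They are not exact error rates for the 5 × 3 ANOVA with Tukey adjustment, which shares the independence assumption. The plan should be changed, but nothing here invalidates the design.

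**What to change.** 1. Record a class identifier for every participant taught in a class, including the education-only arm if it is taught that way. Record the therapist too, for a sensitivity analysis, and state whether therapists work in one arm or several.
2. Replace the repeated-measures ANOVA for CPM and the secondary outcomes by a linear mixed model for group by time. Include participant-level correlation over visits, a random class intercept only in the arms taught in classes, and small-sample degrees of freedom. Let the class term act on the post-baseline visits: classes do not exist at baseline, and an intercept constant over all visits would cancel out of the change from baseline.
3. Restate the power in Sample size {14} over ICC 0.01–0.10, allowing for dropout within classes.
4. Clarify how the abstract's description of the sessions fits with small-class delivery.

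The cost is two data fields and a changed model statement. No patients need be added if the lower power is accepted. Keeping 87% at ICC 0.05 in the main case would need 30 × 1.164 = 34.9, so 35 completers, or 35/0.70 = 50 recruited per exercise arm instead of 43. The downsides are a less favourable power statement and a class-variance estimate that rests on few classes.

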**Fig. 2 Fig2:**

**A** Isolated transversus abdominis and lumbar multifidus training. **B** Progression of training of core muscles—lumbar stabilizing muscle activation in light dynamic functional tasks. **C** Progression of training of core muscles—lumbar stabilizing muscle activation in heavy dynamic functional tasks

Group 3 (SS group): In this group, exercises will be focused on strengthening the rectus abdominis (RA), abdominus obliquus internus (OI), abdominus obliquus externus (OE), and erector spinae (ES) [35]. Each of the exercises will include 3 sets of 15 repetitions lasting for 45–60 min per session. Each exercise will include eight levels of steadily increasing difficulty, as outlined by Koumantakis et al. (2005) [36] (Fig. 3). Exercise progression will be based on the participant’s correct performance of the previous exercise stage and the principles of graded exposure exercise [37]. If the participants were unable to advance, they would continue exercising at the same intensity level.

**Fig. 3 Fig3:**

Abdominal and spine extensor muscle strengthening training

Group 4 (patient education group): Health education sessions will be conducted for these participants twice a week for 12 weeks. Patient education aims to increase patients’ understanding of CLBP and alleviate myths about this condition, reassure them of the ailment’s good prognosis, and offer them useful methods for self-managing their LBP and preventing recurrence and healthcare dependency. The lecture will be followed by a 10-min discussion [38].

After the application of the study intervention, the participants will be instructed to continue the exercise interventions provided at home, twice a week, and to avoid immobility. They will be asked to report their participation using a home exercise diary.

#### Criteria for discontinuing or modifying allocated interventions {11b}

Any changes to the protocol that may affect the conduct of the study, or the potential benefit or safety of the patient, including changes to the study’s objectives, design, patient population, sample sizes, or significant administrative aspects, will necessitate a formal amendment to the protocol after agreement from the Institutional Review Boards of the Integral University and Composite Regional Centre for Skill Development, Rehabilitation, and Empowerment of Persons with Disabilities in accordance with local regulations.

#### Strategies to improve adherence to interventions {11c}

All participants will be periodically followed up over telephone. Face-to-face adherence reminder will be provided during therapy sessions or outcome measurement. The participants will be reminded about the following:Importance of adhering to study guidelines.Instructions about interventions, dosages, and the procedure to be followed in case of a missed session.Instructions about assessment and the procedure to be followed in case of a missed session.Instructions about adverse events expected, if any.Instructions about management of adverse events.Telephonic follow-up will be conducted on days 3 and 5 if the patient fails to show up for the scheduled assessment and intervention sessions.Importance of continuing exercises after the study period and maintaining a treatment diary.

Reasons for missing the sessions will be recorded, and strategies for incorporating exercises into everyday activities will be emphasized. From the time of recruitment, the participants will be encouraged to ask any questions, and their queries will be satisfactorily answered.

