### Trial design {8}

This is a randomized, controlled, double-blinded study determining how CPM changes in response to three types of active exercises in CS-positive CLBP patients. Participants will be randomized to undergo 12 weeks of the motor control exercise (MCE), superficial strengthening (SS), or AE combined with patient education or patient education alone. This active treatment concurrent control design will be used to demonstrate superiority of one exercise group over another. All patients will be allocated in a 1:1:1:1 ratio using random number tables. All participants will receive advice to stay active. Another no-pain control group will also be recruited. The intervention will be provided for 12 weeks. An independent assessor will collect data at baseline (t0), after intervention at 3 months (t1), and at the 6-month follow-up (t2). Outcome measures include CPT for measuring CPM, letter–number sequencing subtest in the Wechsler Adult Intelligence Scale-III Edition (WAIS-III), Stroop neurophysiological test, QoL assessed using the abbreviated WHOQOL-BREF questionnaire, isometric muscle strength of spine and hip muscles, the Oswestry Disability Index (ODI) questionnaire, and the Numerical Pain Rating Scale (NPRS). Table 1 and Fig. 1 present the study design and flowchart, respectively. The research ethics approval was granted by the Integral University, India (IIAHSR/DO/PT/2022/23), and Composite Regional Centre for Skill Development, Rehabilitation, and Empowerment of Persons with Disabilities, India (CRCL/Ph.D. Data Collection/2021–22/1556). The study is designed according to the Consolidated Standards of Reporting Trials (CONSORT) guidelines and reported according to the Standard Protocol Items: Recommendations for Interventional Trials (SPIRIT) checklist. The study will use a 5 (between subjects − type of exercise interventions: MCE vs. AE vs. SS vs. patient education vs. no-pain control) × 3 (within subjects − time: before vs. after vs. 3 months after the intervention) mixed design.

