### Assignment of interventions: blinding

#### Who will be blinded {17a}

The present study is designed as a randomized controlled trial. The intervention groups will be blinded from one another and outcome assessors. All outcome measures will be determined by an independent researcher blinded to treatment allocation. The assessor will attend training sessions on assessment procedures where the proposed assessment methods will be discussed in detail. The participants will be instructed to not disclose their intervention allocation to the outcome assessor. They will be informed that the effect of different active exercise programs will be evaluated so that they are unaware of any expected treatment group benefit. Another experienced researcher will feed the collected data into the computer. The researcher conducting the statistical analysis will not be present when the measurements are taken. All physiotherapists providing interventions will be blinded to the results of evaluations, measurements, and questionnaires.

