### Data collection and management

#### Plans for assessment and collection of outcomes {18a}

All participants will be allotted unique study identifiers independent of any external source data. Using paper forms, data will be initially collected during one-on-one sessions with the participants. All data will be collected in a face-to-face interaction and stored in a secured location. The research team will collaboratively manage the data, and a statistical analyst unaware of the grouping situation or intervention measures will analyze the data.

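### Adherence reminders that can reveal the arm may be given at outcome visits, and nothing keeps them away from the blinded assessor, so blinding is at risk at t1 and t2

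*Protocol article*

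**What the plan says.** Under Strategies to improve adherence to interventions {11c}, two kinds of contact are planned: periodic telephone calls to all participants, and a face-to-face reminder. For the second the article says: "Face-to-face adherence reminder will be provided during therapy sessions or outcome measurement". The list of topics that follows includes "Instructions about interventions, dosages, and the procedure to be followed in case of a missed session" and "Importance of continuing exercises after the study period and maintaining a treatment diary". It does not separate topics for therapy sessions from topics for outcome visits.

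Under Who will be blinded {17a}: "All outcome measures will be determined by an independent researcher blinded to treatment allocation". The stated safeguard is that "The participants will be instructed to not disclose their intervention allocation to the outcome assessor".

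Trial design {8} has an independent assessor collecting the data at t0, t1 and t2. Plans for assessment and collection of outcomes {18a} says that "data will be initially collected during one-on-one sessions with the participants", and adds: "All data will be collected in a face-to-face interaction and stored in a secured location".

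**The concern.** Participants know whether they walk on a treadmill, do motor control or strengthening exercises, or attend lectures only, and therapists know what they deliver. The blinded assessor is therefore the main remaining protection against detection bias. A conversation about a participant's own intervention and dosage can hardly avoid showing the arm. If it takes place at the outcome visit with the assessor present, telling participants not to disclose their arm no longer protects the blind, because the trial's own staff have raised the subject.

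Several outcomes give the examiner room to influence the result:

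- **Pressure pain threshold**, from which conditioned pain modulation is calculated: force is raised at 1 kgf/s until the participant reports pain.
- **Letter–number sequencing**: the researcher marks each item right or wrong.
- **Stroop**: each subtask is timed with a stop clock.
- **Gluteal strength tests**: the participant works against the examiner's hand.

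**Working it through.** No figure in the plan depends on this point, so the main check is a comparison of the relevant sections.

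1. **Can the reminder reveal the arm?** Yes. Its topics include intervention and dosage, and the four randomised arms differ in exactly these (Intervention description {11a}). Other topics, such as following study guidelines or attending assessments, are neutral.
2. **Can it be given at an outcome visit?** Yes. Outcome measurement is one of two named settings. The other, therapy sessions, ends with the 12-week programme. After that, the home phase with its exercise diary begins, and the only face-to-face contacts the article describes are the outcome visits.
3. **Who is there?** The only person placed at those visits is the independent assessor (Trial design {8}; Who will be blinded {17a}), and data are collected one to one ({18a}).
4. **Is the reminder kept apart from the assessor?** No section names who gives it, where, or in what order relative to testing. The non-disclosure instruction is addressed to participants, not to staff giving reminders.
5. **Which visits are exposed?** At t0 no arm can be revealed if the visit precedes randomisation, which the order of events in {11a} suggests. That leaves t1 and t2. A reminder given after testing at t1 would still inform an assessor who also measures t2, and the statistical section judges clinical significance by whether the 10% change holds at 6 months.

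**Illustration with an assumed bias.** The inputs are the plan's own (Sample size {14}): SD 100 kPa, difference 80 kPa, 30 per group, two-sided 5%, 30% dropout.

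- Standard error with 30 per group: 100 × √(2/30) = 25.8 kPa.
- Power by the normal approximation: Φ(80/25.8 − 1.96) = 0.873. The exact t-test gives 0.861. The plan states 87%.
- Recruitment: 30 / 0.70 = 42.9, so 43, as stated.

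The plan's figures reproduce. Now suppose there is no true difference but the assessor introduces a bias b between two arms. The chance of a significant result is 1 − Φ(1.96 − b/SE) + Φ(−1.96 − b/SE). For b = 20 and 30 per group, b/SE = 0.775 and the result is 12.1%. With 43 per group, SE = 100 × √(2/43) = 21.6 kPa.

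| Assumed bias (kPa) | 30 per group | 43 per group |
|---|---|---|
| 0 | 5.0% | 5.0% |
| 10 | 6.7% | 7.5% |
| 20 | 12.1% | 15.3% |
| 30 | 21.3% | 28.5% |
| 40 | 34.1% | 45.8% |

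The document gives no basis for choosing a row. The table shows only how sensitive the comparison is, not what will happen.

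**The case against.** The strongest reply is that the text is permissive and names nobody. Reminders may be given at therapy sessions or at outcome measurement, so both sections can be followed: a therapist can give the reminder in a session, or a non-assessor can give it in another room. This stands. A reader might infer that the plan breaks the assessor blind, or that the two sections contradict each other outright. The document supports neither reading, because no section says that the assessor gives or hears the reminder.

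It can also be said that the topic list covers reminders in general, and that by t1 supervised dosage and missed sessions have largely lapsed. This stands in part. Continued exercise and the diary remain live topics at t1, and nothing confines outcome visits to the neutral items.

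A third reply is that a journal article leaves staffing detail to the full protocol. That would answer a complaint about silence. Here the article itself names outcome measurement as a setting while elsewhere relying on a blinded assessor at the same visits.

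A reader might also try to size the bias from the algometer: at 1 kgf/s, stopping 0.2 to 0.3 s late adds 0.2 to 0.3 kgf to a reading. That does not carry over to conditioned pain modulation, which is the threshold after the cold pressor test minus the threshold before. A constant delay d cancels: (post + 1 × d) − (pre + 1 × d) = post − pre. Bias needs a delay that differs between the two readings and also differs by arm. Nor does the article say whether the force is controlled by hand.

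**Conclusion.** The point holds as a risk that the plan permits. Reminders able to reveal the arm may be given at visits where the blinded assessor is the only person described, and no separation is stated. The exposure is at t1 and t2, for the 172 randomised participants, to the extent that the outcome-visit setting is used with the assessor present. It concerns the examiner-dependent measures, including the primary one; self-completed questionnaires are less affected.

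This rests on two assumptions: that t0 precedes randomisation, and that no arrangement outside the article already keeps reminders away from the assessor. The size of any bias cannot be derived from the document. Power and sample size are unaffected. The point is still worth acting on, because unblinding that goes unrecorded at t1 or t2 cannot be repaired in the analysis.

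**What to change.** Either of two changes to {11c} is enough:

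- Delete outcome measurement as a setting for face-to-face reminders.
- Or state that reminders, diary checks and discussions of missed sessions are handled only by treating therapists, or by telephone by staff who do not assess outcomes; that this is never done by or in front of the assessor; and that the assessor does not see the diary.

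Moving the reminder to after testing is not enough if the assessor is present, because the same assessor may measure t2. A matching line in {17a} would make the duty fall on staff as well as participants.

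The cost is one or two sentences. Therapists and telephone contact with all participants are already in the plan, so no new contact is needed. The small downside is that the face-to-face reminder at the outcome visit is lost or must be given by someone other than the assessor. The planned telephone follow-up can cover the home phase.
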